### Study duration

In the pilot study, 90% of eligible women agreed to participate. Women will be recruited between September 2018 and September 2021 with clinical outcome data collected until March 2022. To achieve the recruitment target of ~2000 women, approximately 20 women will be recruited per week across the seven hospital sites. A temporary pause on recruitment to the study was initiated in March 2020 because of the COVID-19 pandemic. Recruitment recommenced in June 2020 but with COVID-19 restrictions in place, meaning that recruitment rate is slower than pre-pandemic (approximately 10 women per week across recruitment sites).

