### Reference standard

The reference standard is histology where endometrial tissue is collected for routine diagnostic and staging purposes. The hysterectomy specimen will be used in preference to the endometrial biopsy, where available within 3 months of endometrial biopsy and where there was no treatment with neoadjuvant chemotherapy or hormone therapy. Histology results will be classified as inadequate, benign, atypical hyperplasia and endometrial cancer (of any histological subtype or grade). For the primary analysis, a histological diagnosis of endometrial cancer will be considered a positive result. We will report overall results as well as a breakdown by histological subtype and stage of disease. Hyperplasia and benign endometrium will be considered a negative result. In secondary analyses, cancers of other pelvic sites (cervix, vagina, uterus, ovary, fallopian tube, bladder, kidney or bowel) will be considered a positive result. We will record cases of atypical hyperplasia and their cytological interpretation. In cases where an endometrial biopsy is not indicated (endometrial thickness <4 mm and/or normal hysteroscopy) or fails (inadequate sample), the reference standard will be discharge from diagnostic workup. Passive clinical follow-up of negative women will ensure missed diagnoses of endometrial cancer are minimised. This will involve monitoring for any subsequent rereferrals to our service. A diagnosis of endometrial cancer within 3 months of initial discharge from diagnostic workup will be considered a positive clinical result.

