Analysis of the primary objective will compare the clinical performance of cytology with the reference test. Thus, sensitivity, specificity, NPV, positive predictive value and diagnostic accuracy will be reported together with their corresponding 95% CIs, calculated using the exact binomial method. Where a histology result is not available, endometrial thickness <4 mm (histology not indicated) or discharge from diagnostic workup will be used as reference standard. Analysis of the secondary objectives will assess clinical performance of the urine test alone and the vaginal test alone for the detection of endometrial cancer in relation to the reference test. The clinical performance of urine and vaginal cytology for the detection of any cancer affecting the pelvic organs will also be calculated. Secondary analyses will follow the same approach as the primary analysis. Sensitivity analyses will consider the clinical performance of cytology with a broader definition of a positive cytology result (including glandular results as test positives). Interobserver agreement between the cytopathologists will be assessed using the kappa statistic and categorised as poor, fair, moderate and good. McNemar’s χ^2^ test will be used to compare urogenital cytology with routine diagnostics. Multivariate logistic regression will evaluate the relationship between positive cytology and endometrial cancer diagnosis while adjusting for potentially predictive clinical characteristics like age and BMI. The diagnostic accuracy of urogenital cytology will be compared with individual elements of the standard diagnostic pathway, including TVS, hysteroscopy and endometrial biopsy. Consideration will be given as to where in the current diagnostic pathway for endometrial cancer urogenital cytology fits. Its use as a triage test prior to any other diagnostic workup both alone and in combination with clinical parameters (eg, age and BMI) will be modelled. We will also consider its usefulness in combination with transvaginal ultrasound scanning at various endometrial thickness cut-offs. The acceptability of urogenital sampling will be compared with transvaginal ultrasound, hysteroscopy and endometrial biopsy (online supplemental appendix 1).

10.1136/bmjopen-2021-050755.supp1Supplementary data

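### Endometrial cancers found more than 3 months after discharge stay reference-negative by default with no analysis of them, and the hysterectomy-first rule leaves discordant specimens badly defined

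*Protocol article*

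**What the plan says.** Where biopsy is not indicated or yields an inadequate sample, the *Reference standard* section states that "the reference standard will be discharge from diagnostic workup". It then gives follow-up a purpose, "Passive clinical follow-up of negative women will ensure missed diagnoses of endometrial cancer are minimised", and a mechanism, "This will involve monitoring for any subsequent rereferrals to our service". The classification rule for later diagnoses is "A diagnosis of endometrial cancer within 3 months of initial discharge from diagnostic workup will be considered a positive clinical result". Nothing is said about a diagnosis after that point.

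*Study duration* sets the calendar: "Women will be recruited between September 2018 and September 2021 with clinical outcome data collected until March 2022".

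For women with two specimens, *Reference standard* says "The hysterectomy specimen will be used in preference to the endometrial biopsy, where available within 3 months of endometrial biopsy", on condition that no neoadjuvant chemotherapy or hormone therapy was given. The same section makes histological endometrial cancer positive without naming the specimen, and codes hyperplasia and benign endometrium as negative.

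*Statistical analyses* restates the fallback for women with no histology result: "endometrial thickness <4 mm (histology not indicated) or discharge from diagnostic workup will be used as reference standard". It does not repeat the late-diagnosis rule.

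**The concern.** Cytology is proposed as a rule-out test, so the results that matter most are sensitivity and NPV, and both depend on how missed cancers are counted. If a woman with negative cytology is discharged without histology, then re-referred and diagnosed at month 5, the study may hold that diagnosis and still analyse her as a true negative. The protocol gives no reason for choosing 3 months and states no analysis that uses the later outcomes it plans to collect.

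The direction is not neutral. Under *Handling of discordant results*, cytology is reported weekly where possible. When it is positive and the pathway is incomplete, the responsible clinician is asked to consider further tests. Cytology-negative women get no such prompt. Cytology-positive cancers should therefore tend to surface early, leaving the late ones more often cytology-negative.

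The specimen rule raises a second classification problem. Polyps are resected during work-up (*Clinical diagnostic pathway*), so a cancer on biopsy with no residual tumour at hysterectomy is possible. The preference makes no exception for it.

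**Working it through.** **Time available.** September 2021 to March 2022 is about 6 months (5 to 6, depending on the days); September 2018 to March 2022 is about 42 months. These run from recruitment. The 3-month rule runs from discharge, so the real margin is shorter by the length of the work-up, which the article does not give.

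**The plan's own figures** (*Sample size*: 2000 women, 5% prevalence, 85% sensitivity and specificity).
- Cases: 2000 × 0.05 = 100, of whom 85 are true positives and 15 false negatives.
- Non-cases: 1900, of whom 1900 × 0.85 = 1615 are true negatives.
- Sensitivity half-width: 1.96 × √(0.85 × 0.15 / 100) = 7.0 points, as stated.
- Test negatives: 1615 + 15 = 1630, as stated.
- NPV: 1615/1630 = 99.08%. The Wilson interval, 98.5% to 99.4%, matches the stated one.

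**Late cancers.** Let *k* women coded negative have cancer diagnosed after 3 months, *m* of them cytology-positive. Counting them as cases gives sensitivity (85 + *m*)/(100 + *k*) and NPV (1615 − (*k* − *m*))/1630. The article gives neither *k* nor *m*; both are assumptions.

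| *k* | Sensitivity, *m* = 0 | NPV, *m* = 0 | Sensitivity, *m* = *k* |
|---|---|---|---|
| 0 | 85/100 = 85.0% | 99.08% | 85.0% |
| 1 | 85/101 = 84.2% | 1614/1630 = 99.02% | 86/101 = 85.1% |
| 3 | 85/103 = 82.5% | 1612/1630 = 98.90% | 88/103 = 85.4% |
| 5 | 85/105 = 81.0% | 1610/1630 = 98.77% | 90/105 = 85.7% |
| 10 | 85/110 = 77.3% | 1605/1630 = 98.47% | 95/110 = 86.4% |

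A mixed case, *k* = 5 with *m* = 2, gives 87/105 = 82.9%. When *m* = *k*, NPV does not change. Exact 95% intervals for sensitivity are 76.5% to 91.4% at *k* = 0, 72.1% to 88.0% at *k* = 5 and 68.3% to 84.7% at *k* = 10 (both with *m* = 0). Sensitivity falls only if fewer than 85% of the late cancers are cytology-positive.

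**Discordant specimens.** Suppose *j* of 100 true cases, with true sensitivity 85%, are coded negative because hysterectomy shows no residual tumour.
- All cytology-negative: reported sensitivity is 85/(100 − *j*), so 85/99 = 85.9% for *j* = 1 and 85/95 = 89.5% for *j* = 5.
- All cytology-positive: (85 − *j*)/(100 − *j*), so 84/99 = 84.8% and 80/95 = 84.2%.

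The reverse case is atypical hyperplasia on biopsy with cancer at a hysterectomy more than 3 months later. The hysterectomy falls outside the preference, so the biopsy stands and is negative. The late-diagnosis rule counts from discharge and does not clearly cover her. If she was cytology-positive she becomes a false positive; if negative, a true negative. Here too the direction depends on cytology.

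**The case against.** A fixed window is a legitimate way to separate cancer present at sampling from cancer arising later, and it treats early and late recruits alike despite unequal follow-up. That stands, and it is why the primary window need not change. A reader might want 6 months instead, but the article supports that no better than 3, and women recruited in late September 2021 may not reach it.

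The article never says that a cancer after 3 months is negative. True: that is the default, because the only reversing rule does not reach it. Follow-up is also passive, so only re-referred cancers would be known.

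A reader might infer that *Statistical analyses* contradicts *Reference standard*, making a woman with endometrium below 4 mm and a cancer at 2 months negative in one and positive in the other. The text does not support this. The fallback applies only when no histology result exists, and a histologically diagnosed cancer supplies one. All that remains is that the late-diagnosis rule is not repeated there.

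Nor are all these women left unverified or dependent on passive follow-up. Inadequate biopsies lead to hysteroscopy under general anaesthesia, and cytology-positive women with an incomplete pathway are flagged. The gap is mainly among cytology-negative women.

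On specimens, the sentence making histological cancer positive can be read as overriding the preference. The article therefore does not state flatly that biopsy-proven cancer is negative; its rules leave the case open. An unrestricted either-specimen rule would also go wrong for enriched women sampled after a diagnostic biopsy, for whom absence of residual tumour may be the truer status at sampling.

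**Conclusion.** The concern holds in a limited form. Cancers found on re-referral after 3 months in women without histological verification remain reference-negative by default, although outcome collection runs well past that point for most recruits, and no analysis of them is stated. Given the one-sided prompt for further tests, sensitivity and NPV would tend to be overstated by about 0.8 and 0.06 points per cytology-negative late cancer. One or two such cancers would matter little; ten would move sensitivity by 7.7 points, more than the planned ±7. That figure is the extreme of an assumed range and should not be read as an expectation. If the late cancers were cytology-positive at the planned 85%, sensitivity would not move.

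The specimen rule is a second defect, resting on a literal reading. It is tempting to say that every part of the reference standard favours the test, but the specimen rule can bias sensitivity in either direction (84.2% to 89.5% for up to five residual-free cases).

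**What to change.** - Keep a fixed window for the primary analysis and state how a cancer diagnosed after it is classified.
- Pre-specify a sensitivity analysis that counts every endometrial cancer known from re-referrals by March 2022 as reference-positive.
- For women sampled before biopsy, define the reference as positive if either biopsy or hysterectomy shows endometrial cancer, and use the hysterectomy for subtype and stage. Handle enriched women sampled after a diagnostic biopsy separately.
- Repeat the late-diagnosis rule of *Reference standard* in *Statistical analyses*.

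The cost is a few sentences and one further analysis, on data the study already plans to collect. The downside is small: some cancers that arose after sampling may count as missed in the sensitivity analysis.

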### Blinding

In most cases, research samples will be collected prior to routine diagnostic workup, and sample takers will be blinded to participant cancer outcomes. If the proportion of cases is less than 5% at the midpoint of the study, the cohort will be enriched with endometrial cancer diagnoses by recruiting higher-risk women (endometrial thickness >4 mm on TVS) and those with proven endometrial cancer prior to hysterectomy. Care will be taken to collect research samples at least 7 days after any diagnostic uterine instrumentation. The cytology team will always be blinded to the cancer status of participants when performing cytological review of urine and vaginal samples. They will have no access to clinical data or results of routine diagnostic tests. Individual participants will not routinely receive their cytology results.

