### Participants and recruitment

Consecutive women will be recruited from gynaecology clinics at seven hospital sites across the North West England: St Mary’s Hospital, Trafford General Hospital, Wythenshawe Hospital, Royal Oldham Hospital, North Manchester General Hospital, Fairfield General Hospital and Tameside Hospital.

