### Sample size

With a sample size of ~2000 women and an endometrial cancer prevalence of 5%,^5^ there will be approximately 1900 women without endometrial cancer and 100 women with endometrial cancer. The study will have 80% power to determine the sensitivity of the test at ≥85%±7% and the specificity of the test at ≥85%±2%. At 85% specificity, around 1630 women will have a negative test result, giving the test a NPV) of 99.1% (98.5% and 99.4%). These estimates originate from the pilot study, where sensitivity and specificity were both >85%. The prevalence of endometrial cancer will determine the final sample size. If the prevalence of endometrial cancer is greater than 5%, fewer than 2000 women will be needed; if it is less than 5%, more women will be needed to determine the sensitivity of the test at ≥85%±7%.

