### Index tests

The timing of urine and vaginal sampling is important to ensure validity of the results. Both research samples will be taken before any routine clinical procedures to avoid inadvertent contamination with iatrogenically dislodged endometrial cells (study schema, figure 1). Of the two research samples, urine will be collected first because vaginal sampling will remove naturally shed uterine debris from the lower genital tract and affect interpretation of the results.

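### If the low-prevalence enrichment rule fires, PPV, NPV and overall accuracy would reflect a case mix set by the design, because the protocol gives no separate analysis by recruitment route

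*Protocol article*

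**What the plan says.** All references are to the protocol article.

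- **Participants and recruitment** gives the sampling frame: "Consecutive women will be recruited from gynaecology clinics".
- **Index tests** gives the order of sampling, and treats it as a matter of validity: "Both research samples will be taken before any routine clinical procedures".
- **Sample size** assumes 5% prevalence, so that "there will be approximately 1900 women without endometrial cancer and 100 women with endometrial cancer". Its answer to lower prevalence is that "if it is less than 5%, more women will be needed".
- **Blinding** gives another answer. If cases are under 5% at the midpoint, "the cohort will be enriched with endometrial cancer diagnoses by recruiting higher-risk women" (ET above 4 mm on transvaginal sonography, TVS) and women with already proven cancer before hysterectomy. It adds that care will be taken to sample at least 7 days after diagnostic uterine instrumentation. The section opens by saying that sampling precedes workup in most cases, so it allows exceptions.
- **Secondary outcome measures** defines PPV and NPV as simple proportions of women testing positive or negative.
- **Statistical analyses** says that "sensitivity, specificity, NPV, positive predictive value and diagnostic accuracy will be reported together with their corresponding 95% CIs", by the exact binomial method. It mentions no split by recruitment route, no restriction to consecutive women and no reweighting to natural prevalence. It also plans comparisons of cytology with TVS and with ET cut-offs.

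**The concern.** The study is meant to support a rule-out triage test for women presenting with postmenopausal bleeding. PPV and NPV depend on prevalence. After enrichment the investigators set that prevalence, because recruitment then depends on a TVS result or on the outcome itself. Overall accuracy is a prevalence-weighted mean of sensitivity and specificity, so it inherits the same problem whenever the two differ.

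Two further effects are possible:

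- The Introduction names polyps and atrophy as benign mimics that make cytology hard to read. Non-cancers selected on ET may therefore have a different false-positive rate.
- Proven cases will generally have been instrumented before sampling, and Index tests treats sampling order as important for validity.

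Selecting women on ET also selects them on the comparator in the planned TVS analyses.

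Separately, four sections give incompatible accounts of who is recruited, when samples are taken, and what happens if prevalence is low.

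**Working it through.** **Inputs.** From Sample size: N about 2000, 5% prevalence (100 cancers, 1900 non-cancers), sensitivity and specificity 85%. From Blinding: trigger under 5% at the midpoint. Assumed: the midpoint is 1000 women, and enrichment brings the final cohort to 5%. The protocol states neither.

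**1. The plan's own figures.** The half-width is 1.96·√(p(1−p)/n).
- Sensitivity: 1.96·√(0.85·0.15/100) = 7.0 points.
- Specificity: 1.96·√(0.85·0.15/1900) = 1.6 points, which rounds to the stated 2.
- Negatives: 0.85·1900 + 0.15·100 = 1630.
- NPV: 1615/1630 = 99.08% (Wilson 98.49% to 99.44%), matching the stated 99.1% (98.5%, 99.4%).

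The stated NPV is therefore the value at a prevalence of exactly 5%.

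**2. How often the trigger fires.** P(X ≤ 49) for X binomial with n = 1000:

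| True prevalence | P(trigger) |
|---|---|
| 4% | 93% |
| 4.5% | 76% |
| 5% | 48% |
| 5.5% | 23% |
| 6% | 8% |
| 7% | 0.4% |

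**3. Predictive values.** With prevalence π:
- PPV = Se·π / [Se·π + (1−Sp)(1−π)]
- NPV = Sp(1−π) / [Sp(1−π) + (1−Se)π]

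| π | PPV | NPV |
|---|---|---|
| 5% (enriched cohort) | 0.0425/0.1850 = 23.0% | 0.8075/0.8150 = 99.08% |
| 4% | 0.0340/0.1780 = 19.1% | 0.8160/0.8220 = 99.27% |
| 3% | 0.0255/0.1710 = 14.9% | 0.8245/0.8290 = 99.46% |

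Enrichment to 5% overstates PPV by 3.9 points (true 4%) or 8.1 points (true 3%). It understates NPV by 0.19 or 0.38 points.

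**4. Overall accuracy.** Accuracy = π·Se + (1−π)·Sp. At Se = Sp = 85% it is 85% at any prevalence. It moves with case mix only when the two differ.

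**5. Specificity (illustration).** Proven cancers add no non-cancers, so only the ET route can act. Assume that half of all non-cancers come from that route and that 40% to 60% of naturally referred non-cancers have ET above 4 mm. The pooled shift is then:
- 0 if specificity does not vary with ET;
- −1.6 to −2.4 points if it is 88% (thin) and 80% (thick);
- −3.0 to −4.5 points if it is 90% and 75%.

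**6. Sensitivity (illustration).** Assume 85% in consecutive cancers and 40 to 70 of 100 cancers recruited as proven cases. Pooled sensitivity is 78% to 81% if proven cases have 75%, 85% if they have 85%, and 87% to 88.5% if they have 90%. The shift can go either way.

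**7. Section against section.** A woman recruited on her ET has already had TVS, and a woman with proven cancer has already been diagnosed. Neither fits a consecutive series sampled before any routine procedure. Reaching 100 cancers from consecutive women alone would need 100/0.04 = 2500 women at 4%, or 100/0.03 ≈ 3334 at 3%. Recruiting more women and enriching are therefore materially different responses to low prevalence.

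**The case against.** The case against has real force.

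- **Pooling is inferred.** The rule is conditional, this is a condensed article, and an unseen SAP could separate the routes. That stands. The point is limited to what follows if the text is applied as written. A SAP would not remove the conflicts between sections, which concern the sampling frame and design.
- **Contamination is addressed.** Blinding provides a 7-day minimum interval after instrumentation. That stands. Whether it suffices cannot be judged from the document.
- **The certain effect is on secondary outcomes.** PPV and NPV are secondary, and NPV, which matters most for ruling out, moves conservatively. That stands and limits the harm.
- **Large distortions need low prevalence.** The Introduction cites 5% to 10%. At a true prevalence of 5%, enrichment to 5% changes little, so the 48% trigger probability must not be paired with the PPV figure for 3%. That also stands. However, Sample size and Blinding both plan for prevalence below 5%, and at 4% the rule would almost certainly fire.
- **More women need not mean consecutive women.** This is a fair reading of Sample size, but that section does not mention selective recruitment, so the two still need aligning.

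A reader might go further and infer that sensitivity and specificity are shown to be biased, for example that proven cases would carry the sensitivity past 85%. The document does not support this: any difference by route is an assumption, and its direction is open. Nor does the amendment table's approval to recruit proven cases (V4.3) show that enrichment took place.

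**Conclusion.** The point holds in conditional form. If enrichment occurs and the single analysis is applied to the whole cohort, PPV and NPV reflect a prevalence set by the design. At 85% sensitivity and specificity and enrichment to 5%, PPV is about 4 points too high at a true prevalence of 4% and about 8 points too high at 3%. NPV is 0.2 to 0.4 points too low. Overall accuracy is affected only as far as sensitivity and specificity differ.

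For sensitivity and specificity there is a plausible spectrum risk of unknown size and direction, which is zero if cytology performs equally across routes. The figures assume a midpoint of 1000 women and a 5% enriched cohort. A higher enriched proportion would enlarge the gap.

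The inconsistency between the four sections does not depend on any of these assumptions.

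**What to change.** 1. Record recruitment route for every participant (consecutive and sampled before workup; ET above 4 mm; proven cancer) and show it in the STARD diagram.
2. Estimate specificity, PPV, NPV, overall accuracy, prevalence and any comparison with TVS or ET cut-offs only in consecutive women sampled before workup. Alternatively, compute predictive values by Bayes' rule at the consecutive-cohort prevalence.
3. Report sensitivity for consecutive, enriched and pooled cases, and state which is primary before cytology results are unblinded for the accuracy analysis.
4. Reconcile Participants and recruitment, Sample size, Index tests and Blinding on sampling frame, response to low prevalence, and timing of samples.

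**Cost.** One data field and some analysis wording, plus some precision. If all recruitment after the midpoint were enriched, about 960 consecutive non-cancers would remain at 4% prevalence. The specificity half-width would then be 1.96·√(0.85·0.15/960) = 2.3 points, against 1.6 with 1900.

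Making consecutive-only sensitivity primary is a genuine trade-off and not a requirement. With 60 cancers the half-width is 1.96·√(0.85·0.15/60) = 9.0 points, which misses the planned 7. The exact interval for 51/60 is 73.4% to 92.9%, against 76.5% to 91.4% for 85/100. Pooled sensitivity as primary, with the breakdown by route beside it, is defensible if chosen in advance.
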